**Research Protocol for Strength Training Intervention for Hybrid Workers: A Randomised Pilot Feasibility Trial**

**Project Summary**

Since the COVID-19 pandemic, working practices for office-based employees have changed significantly, where working from home having increased. This change in working practices has, however, affected employees’ lifestyle behaviours and health and wellbeing. There is a major productivity and economic loss due to poor mental and physical health of the workforce. Home-based muscle strengthening interventions designed specifically for the hybrid working employee population are needed, as they can improve these factors. Therefore, this study aimed to investigate the effect of a time-efficient, resistance band training intervention for hybrid working employees on physical function and work-related outcomes.

This project is a pilot randomised controlled trial, involving untrained hybrid-working employees who will be randomised to a four-week resistance band training intervention (15 mins 3x per week) or control group. Written and video instructions on the exercises were provided. The primary outcomes were physical function; 30s sit-to-stand and 30s push-up test, with secondary outcomes of perceived stress, work engagement and productivity. Outcome data was collected via an online survey. All of the physical function tests and online surveys will be conducted remotely from the participant’s home.

This study is expected to generate evidence on the effectiveness of a low-cost, home-based resistance training intervention for improving workplace outcomes and strength. Insights may inform workplace wellness policies and health system strategies by promoting scalable, preventative approaches to physical function and well-being. The results from this study will be presented at scientific meetings, published in scientific journals and used in the research project reports of a master’s student undertaking this research. The results will be disseminated through practical resources for employers and health professionals, supporting real-world application.

**Rationale and Background Information**

The role of strengthening activities in improving and maintaining health are well known and include reducing muscle loss (both quality and quantity), falls prevention and bone strengthening (Warburton et al. 2017). However, only 31% of men and 24% of women in the UK meet both the aerobic and strength/resistance guidelines (Scottish Health Survey 2017). Many barriers to resistance training have been reported, including time constraints and access to a gym. With the shift to home/hybrid working, home-based resistance training programs using resistance bands, which can be purchased at a low cost, and body weight exercises may be an effective strategy to help increase activity levels.

To date, resistance band programs in home-working adults is yet to be explored. Positive effects of similar programs have been reported in different populations, such as older adults (Orange et al. 2019) and can produce similar benefits to weight training (Lopes et al. 2019). Outcomes of interest to workplaces, such as burnout and stress have can also be positively influenced, but this has not yet been tested in home-based employees. Therefore, a low-volume, home-based resistance training intervention will be developed and investigated to see if this can have positive benefits to work-related outcomes and strength.

Reference:

- The Scottish Government. Scottish Health Survey 2018: main report - revised 2020 2020 [Available from: <https://www.gov.scot/publications/scottish-health-survey-2018-volume-1-main-report/>

**Study Goals and Objective**

The aims of this study are to:

- Develop a low-volume, low-cost home-based resistance training intervention
- Compare the effects of the intervention to a control on workplace outcomes of stress, productivity, work performance and work engagement
- Compare the effects of the intervention to a control on musculoskeletal health
- Compare the effects of the intervention to a control on physical function/strength

**Study Design**

| **Study Design** | This study will utilise Randomised Control Trail (RCT) design. Following completion of the baseline measurements participants will be randomised (stratified by sex) to either a waiting list control or exercise intervention group. The control group will be asked to maintain their habitual activity and will be offered the intervention at the end of the study. Those in the exercise intervention group will all take part in a home-based low volume resistance exercise intervention. All participants will be asked to maintain their normal dietary habits throughout the study. |
| --- | --- |
| **Participants and Recruitment** | Participants will be adults (16 year and older) working from home at least 3 days per week and not currently achieving government strength guidelines of 2 days per week. Participants will not be eligible for this study if they are unable to exercise and will be excluded if they have had prior history of heart, lung, cancer, kidney, endocrine, or liver disease. Participants must pass the physical activity readiness questionnaire (PAR-Q) to be eligible to join the study. Invites to participate in the study will be sent out by the research team through their existing social media channels (Twitter, Facebook) and existing workplace contacts. |
| **Sample Size** | The current study is a pilot RCT study and no formal sample size calculation has been carried out. The main component of the intended work is to collect preliminary data to inform the sample size calculations for a subsequent definitive trial. Sample size is therefore based on guidelines from Julious (2005) suggesting a minimum of 12 participants per group, with allowance for a 50% drop out per group, meaning 50 employees will be recruited (25 people per group). In order to get a gender balance, males’ participants will be capped at 25 and the recruitment strategy adapted to ask for women only.  Reference: Julious SA. Sample size of 12 per group rule of thumb for a pilot study. Pharm Stat. 2005;4(4):287-91. |
| **Intervention and Development** | The intervention will take place over 4 weeks. The employees will be provided with a set of resistance bands free of charge (~£15). Each person will start with the same bands for the prescribed exercises in week 1. They will be given a range of reps to achieve for each session (8-12). The prescribed band for the 2nd week will be based on the number of reps achieved in the previous week and perceived effort for each exercise. The exercises will be performed once per day 3x/week on days chosen by the participants, with 2 sets in weeks 1 and 2 and 3 sets in weeks 3 and 4. A similar protocol was shown to have positive effects on adults aged 50+ (Orange et al. 2019). The following exercise will be performed: lateral walk, squat, glute raise, deadlift, modified press-up, standing scapula retraction, seated row, core rotation. Exercises will be paired up by muscle group so that participants can complete another exercise whilst another muscles group is resting (e.g. squats and modified press-up). Exercises will be recorded in a short video introduction that participants can watch and rewatch to ensure they are doing them correctly. A project steering group will be created consisting of colleagues and existing contacts of the research team who will refine the final intervention to be delivered. This is largely in relation to the type of activities to be included to ensure they are suitable for performing in work clothes and without needing to shower. Adjustments are likely to include switching of exercises or performing fewer reps and sets – and not increasing the activity detailed above.  Reference: Orange ST, Marshall P, Madden LA, Vince RV. Short-Term Training and Detraining Effects of Supervised vs. Unsupervised Resistance Exercise in Aging Adults. J Strength Cond Res. 2019;33(10):2733-42. |

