| **Statistical Analysis** | Survey data will be exported to Excel (2016), and all statistical analysis will be performed using SPSS version 28.0 software (SPSS Inc., Chicago, IL). A sample size of 30 was determined based on guidelines for feasibility studies by Julious (2005) suggesting a minimum of 12 participants per arm, and allowing for a rate of 20% attrition. No further formal sample size calculations were undertaken due to this being a feasibility study.  Data will be visualised using box plots to check for outliers and then checked for normal distribution. Any missing data will be imputed using the corresponding answer given in their baseline survey answer (last-observation-carried-forward). Demographic data that will be gathered at baseline will be cleaned to condense the number of categories where necessary, so that no category had fewer than 5 people in it. Continuous variables will be presented as mean ± SD, and categorical variables as n (%). A 2x2 mixed ANOVA will be conducted to examine the group x time interaction effects on physical function tests and work-related outcomes. All analyses will be treated as intention-to-treat. Assumptions will be checked for all statistical analyses, and significance will be set at p<0.05. Adherence will be calculated as the percentage of self-reported sessions completed compared to those expected (12 expected sessions). |

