**Problems Anticipated**

Here are the problems anticipated, and the solution planned.

1. Recruitment and potential dropout – Longer recruitment period and potentially paid advertising on social media
2. More males than females – stop recruitment when half sample is males.
3. Potential Covid influence – delivery data collection remotely as planned

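### The protocol gives two contradictory sample sizes, 50 with 50% dropout and 30 with 20% attrition, both built on the same minimum of 12 per arm

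*Protocol*

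**What the plan says.** The number of participants is set in two sections of the protocol, and two other sections depend on it.

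- **Study Design, Sample Size row.** No formal calculation was done. The size rests on a published rule of thumb, "suggesting a minimum of 12 participants per group", with an "allowance for a 50% drop out per group, meaning 50 employees will be recruited (25 people per group"). To balance the sexes, male "participants will be capped at 25 and the recruitment strategy adapted to ask for women only".
- **Data Management and Statistical Analysis, Statistical Analysis row.** The same guideline is cited, again "suggesting a minimum of 12 participants per arm", but here "A sample size of 30 was determined", "allowing for a rate of 20% attrition".
- **Problems Anticipated.** The remedy listed for an excess of males is to "stop recruitment when half sample is males".
- **Budget.** 50 sets of bands at £15.00 each, £750.00 in all. The waiting-list controls are offered the intervention, with its materials, after the trial period (Study Design; Ethics), so both arms may need bands.

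**The concern.** Both statements are current protocol text and both start from the same 12 per arm, yet they give different totals because they assume different losses. The protocol does not say that one replaces the other, or that 50 is a recruitment ceiling and 30 an analysis target. Someone following or auditing the protocol could not say when recruitment is complete.

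Three things depend on the answer:

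- **The basis for the size.** The 12 per arm is the only justification offered for the size of the trial. Whether it is reached depends on the number recruited and the loss together, and neither is settled.
- **The sex mix.** The male cap is written as a fixed number in one section and as a fraction of the sample in another. The two agree for only one of the totals. Sex is the stratification factor, and the push-up test has a different starting position for men and women, so the mix matters.
- **The band order.** The count matches only one of the totals.

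**Working it through.** **Inputs, all from the protocol.** Minimum of 12 per arm (both sections). Dropout d = 0.50 with N = 50, 25 per group (Study Design). Attrition d = 0.20 with N = 30 (Statistical Analysis; the split is not stated there, so 15 per arm assumes equal groups). Male cap 25 (Study Design) or half the sample (Problems Anticipated). Band sets 50 (Budget).

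**Step 1. Reproduce each stated total.** Recruits per arm = 12 / (1 − d).

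- d = 0.50: 12 / 0.50 = 24 per arm, 48 in all. The stated 50 is 2 more, which looks like rounding up to 25 per arm.
- d = 0.20: 12 / 0.80 = 15 per arm, 30 in all. The stated 30 is exact.

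Both totals follow from their own inputs. The difference, 50 − 30 = 20 participants, comes from the difference in assumed loss, 50% − 20% = 30 percentage points.

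**Step 2. Expected completers per arm.** Completers = (N / 2) × (1 − d).

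| N recruited | Loss 50% | Loss 20% |
| --- | --- | --- |
| 50 | 25 × 0.50 = 12.5 (stated pair) | 25 × 0.80 = 20 (crossed) |
| 30 | 15 × 0.50 = 7.5 (crossed) | 15 × 0.80 = 12 (stated pair) |

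Within the stated pairs the result is 12.5 or 12. A value below 12 arises only when the smaller N meets the larger loss.

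**Step 3. Largest loss that still leaves 12 per arm.** Loss = 1 − 12 / (N / 2).

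- N = 50: 1 − 12/25 = 52%.
- N = 30: 1 − 12/15 = 20%.

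A target of 30 therefore has no margin beyond its own assumption.

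**Step 4. Male cap.**

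- N = 50: half the sample is 25, so the fixed cap and the half-sample rule agree (25/50 = 50%).
- N = 30: half the sample is 15. The fixed cap of 25 would allow 25/30 = 83% males.

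**Step 5. Bands.** 50 sets is one per participant at N = 50. At N = 30 it would be 50 − 30 = 20 more than one each.

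**The case against.** The strongest reply is that the design target is the same in both places. Both sections aim at 12 per arm and each stated pair delivers about that number; only the inflation for loss differs. There is no power claim to undermine. This stands, and it limits the point: the protocol contradicts itself, but neither sum contains an arithmetic error. The male cap is likewise not missing. It is stated as 25 and conflicts with the half-sample rule only if 30 is the target.

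Four stronger readings are tempting and are not supported.

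- **That 50 is clearly the true target.** The cap and the band count fit 50, but they do not settle the matter. The figure of 30 is given in the past tense in the analysis section, so it may be the later text. The protocol does not say.
- **That Problems Anticipated would end all recruitment at half males, against the women-only recruitment in Study Design.** The wording is loose, but it is the listed solution to having more males than females. It most naturally means that recruitment of males stops. It needs clarifying and is not a second contradiction.
- **That confidence intervals would widen as if only 7 or so per arm were analysed.** That assumes a comparison of completers only. The protocol plans an intention-to-treat 2x2 mixed ANOVA with baseline values carried forward, so dropouts stay in the analysed number. Precision of the group-by-time interaction also depends on a baseline to follow-up correlation that is not given.
- **That a key pilot endpoint, retention, loses its benchmark.** Retention is not among the stated aims or outcomes, and no progression threshold is set.

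**Conclusion.** The point holds as a contradiction in the current protocol: two recruitment targets 20 participants apart and two loss assumptions 30 percentage points apart, from one minimum of 12 per arm, with nothing to say which governs. A recruitment target is something the trial relies on directly, so this should be corrected even though no formal power calculation hangs on it.

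The linked consequence is firm: the cap of 25 males and the 50 band sets fit only N = 50, and at N = 30 the cap would permit 83% males and defeat the stated aim of gender balance.

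The shortfall to 7.5 completers per arm is a stress test. It takes the N from one section and the loss from the other, assumes equal groups and equal loss, and is not something the protocol plans. It shows why both numbers must be settled together. It does not show that the trial will fall short: a reader might infer that, but either pair taken as stated reaches about 12.

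**What to change.** The sponsor should first determine which target governs, then:

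- State one N and one attrition rate, identically, in the Sample Size row of Study Design and in the Statistical Analysis row of Data Management and Statistical Analysis. If the target was revised, record the date and the reason.
- Set the male cap to half of that N: 25 if the target is 50, 15 if it is 30.
- Clarify in Problems Anticipated that reaching the cap stops recruitment of males only, with women still recruited.
- Align the number of band sets in the Budget with the chosen N.
- If 30 governs, say plainly that 12 completers per arm is reached only if attrition is 20% or less.

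The cost is protocol wording only. Under either consistent pair the expected number of completers stays at about 12 per arm, so the correction does not make the stated design look weaker.

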**Methodology**

[figure not shown]

| **Overview** | Data will be collected through an online survey and physical function tests. For the function tests, participants will either be provided with a video instruction or attend a live, online session with a researcher to see how to preform and score the tests. They will be asked to score their own tests and either email these to the researchers or enter the details into the online survey. All measures will be collected at baseline and after the 4 weeks. Each test/measure are detailed further below. |
| --- | --- |
| **Online Survey** | The survey will include questions on demographics (age, gender, ethnics background, postcode, qualification, general health), Job (employment status, job title, annual income, working from home status, hours worked, physical activity at work), work related outcomes (health related quality of life - HRQL, stress - Perceived Stress Scale, productivity - HWQ, work performance - HPQ short, work engagement - UWES), physical activity (PA levels -GPAQ, days of strength training) and musculoskeletal conditions (Roland-Morris Disability Questionnaire, the Keele STarT Back Screening Tool). In the follow up survey, no demographic data will be collected and instead, open ended questions will be provided for employees to feedback on any improvements or changes to the intervention and protocol. |
| **Push-Up Test** | The test requires participants to complete the maximal amount of push-ups consecutively without rest. Participants will either start on their knees if female or in the standard down position for males. The test will stop when the participant fails to reach the appropriate technique on two consecutive attempts. |
| **30-Second Sit to Stand Test** | The participant is encouraged to complete as many full stands as possible within 30 seconds. As participants will be at home, a stable dining chair will be recommended for the test. The number of stands a person can complete in 30 seconds is counted as the score. |
| **Participation** | Exercise adherence will be measured through weekly check-ins by email asking the participants to report the actual dose achieved compared to the dose prescribed. |

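### The push-up primary outcome pools knee push-ups (women) and standard push-ups (men) as one raw count, so its pooled effect and SD can depend on the sex mix

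*Protocol*

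**What the plan says.** The Project Summary makes the test primary: "The primary outcomes were physical function; 30s sit-to-stand and 30s push-up test". The Methodology section (Push-Up Test) sets the position by sex, "Participants will either start on their knees if female or in the standard down position for males", and describes the score: "The test requires participants to complete the maximal amount of push-ups consecutively without rest". No conversion to a common scale is given. These two sections also differ on whether the test has a time limit. That needs reconciling separately, and nothing below depends on it.

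The Statistical Analysis section states: "A 2x2 mixed ANOVA will be conducted to examine the group x time interaction effects on physical function tests and work-related outcomes". On summaries it states: "Continuous variables will be presented as mean ± SD, and categorical variables as n". It mentions neither a sex factor nor a split by sex nor a standardised score. That both sexes enter as one raw count is inferred from this model; the protocol does not use the word pooled.

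Three statements in Study Design bear on the point. Randomisation is stratified by sex. The pilot's main purpose is to supply data for the sample size of a later definitive trial. On the sex mix, male "participants will be capped at 25 and the recruitment strategy adapted to ask for women only". Problems Anticipated adds that recruitment stops once men make up half the sample. Neither section sets a minimum for men or a maximum for women.

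**The concern.** One repetition is a different task for a woman than for a man. A mean over both sexes is therefore a weighted average of two kinds of count, and the weight is the share of men recruited. The between-arm difference in change is built in the same way.

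This matters because of what the pilot is for. If the two tests differ in level, in spread or in response to training, the pooled effect and SD partly describe the sex mix of this sample. A definitive trial planned from them with another mix could be too small or too large. The protocol already treats sex as important enough to stratify on, yet the stated model does not use it.

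**Working it through.** **The plan's own figures.** Both sample-size statements start from 12 per group.
- Study Design: 12 / (1 − 0.5) = 24 per group, 48 in total, against 25 and 50 stated.
- Statistical Analysis: 12 / (1 − 0.2) = 15 per arm, 30 in total, as stated.

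Both reproduce (the first within 2 people). The two totals disagree with each other, but that is a separate matter.

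**Possible sex mix.** With 50 recruited and at most 25 men, the male share p can lie between 0 and 25/50 = 50%. With 30 recruited, the cap of 25 alone would allow 25/30 = 83%, but Problems Anticipated would stop at half. The intention is plainly about half; the text does not fix it from below.

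**Assumed inputs.** The protocol gives no push-up mean, SD or effect, so every push-up value below is an assumption.

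**Baseline SD.** Let the within-sex SD be 1 in both sexes and let the male and female means differ by D within-sex SDs. Then pooled SD = √(1 + p(1 − p)D²). At p = 0.5:
- D = 0: 1.00
- D = 0.5: 1.03
- D = 1: 1.12
- D = 1.5: 1.25

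This affects the baseline and follow-up SDs. A stable difference in level drops out of within-person change, so the group-by-time test is not affected in this way.

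**Effect on change.** With effects e_m (men) and e_w (women), and SDs of change s_m and s_w:
- pooled effect e = p·e_m + (1 − p)·e_w
- control-arm variance v = p·s_m² + (1 − p)·s_w²
- treated-arm variance = v + p(1 − p)(e_m − e_w)²
- SD = square root of the average of the two variances
- n per arm = 2(1.960 + 0.842)²(SD/e)², for two-sided 0.05 and 80% power. The protocol sets p<0.05; sidedness and power are assumed.

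Worked case: effects 3 (women) and 2 (men), SD of change 4 in both, p = 0.5. Then e = 2.5, v = 16, treated-arm variance = 16.25, SD = √16.125 = 4.02, and n = 15.70 × (4.02/2.5)² = 40.6, so 41.

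| Effect, women / men | SD of change, women / men | n per arm, 0% men | 25% men | 50% men |
|---|---|---|---|---|
| 3 / 3 | 4 / 4 | 28 | 28 | 28 |
| 3 / 2 | 4 / 4 | 28 | 34 | 41 |
| 3 / 1.5 | 4 / 3 | 28 | 33 | 40 |
| 3 / 1.5 | 5 / 3 | 44 | 49 | 54 |
| 2 / 3 | 4 / 5 | 63 | 57 | 52 |

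From 0% to 50% men, n per arm changes by 0% in the first row, by 41/28 − 1 = +46% in the second and by 52/63 − 1 = −17% in the last. Neither the size nor the direction can be read from the protocol.

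**Precision of by-sex results.** With 12 completers per arm and half of them men, there are about 6 per sex per arm. A by-sex SD of change pooled over arms then has 2 × (6 − 1) = 10 degrees of freedom. For normal data its 95% interval runs from about 0.70 to 1.76 times the estimate. For all 24 completers (22 degrees of freedom) it runs from about 0.77 to 1.42 times.

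**The case against.** The case against is substantial.

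- **The arm comparison is protected.** Stratification should give both arms similar shares of each test, and each person presumably repeats the same position. A reader might infer that the treatment comparison is biased; the protocol does not support that.
- **The plan aims for balance.** The cap and the stopping rule both point to about half men, and the imbalance that the protocol anticipates is too many men. A sample with few men is possible under the text but is not suggested by it.
- **Any average effect moves with the sex mix if the sexes respond differently,** sit-to-stand included. That is true, so the table alone does not show a problem of units. For push-ups, however, the protocol itself gives the sexes different tasks, which is a specific reason not to assume equal effects or SDs.
- **Pooled figures are still usable.** A reader might infer that they cannot be taken to another trial at all. A definitive trial with the same test and a similar mix could use the pooled SD of change. Use with a different mix is where caution is needed.
- **Training and testing.** The exercise list reads "lateral walk, squat, glute raise, deadlift, modified press-up, standing scapula retraction, seated row, core rotation". A reader might infer that women train on the movement on which they are tested and men do not, or that many men will score zero. The modified press-up is not defined, the steering group may switch exercises, and nothing in the protocol bears on zero scores. Neither inference is supported.
- **By-sex tables could sit in a SAP that is not shown.** They could, and the Statistical Analysis section does not forbid them. The model that it does name leaves out sex.

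What stands against the point is that its size is unknown and may be zero, and that a complete split by sex would cost precision.

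**Conclusion.** The point holds in a limited form. The protocol defines a primary outcome as two different tests by sex and names a model and summary that treat the result as one raw count. The test of group by time remains unbiased. The pooled effect and SDs can depend on the share of men, and this weakens them as inputs for the definitive trial.

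No size can be stated from the documents. Under the assumptions shown, with the share of men going from none to half, the baseline SD rises by 0 to 25% and the definitive trial's n per arm changes by between −17% and +46%. The change in n is zero if both sexes have the same effect and SD of change; the baseline SD is unaffected if both have the same mean and SD. This is an inexpensive improvement to analysis and reporting. It is not a flaw that invalidates the trial.

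**What to change.** In the Statistical Analysis section, for the push-up outcome:

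1. Add sex, the stratification factor, to the model. It should enter with its interaction with time, since a term for level alone does not touch the comparison of change.
2. Base the combined effect on change standardised within sex, that is, change in repetitions divided by that sex's baseline SD. This gives a common scale; it does not make the two effects equal.
3. Report the mean, the SD and the between-arm difference in change for women and for men, descriptively, beside the pooled raw figure, and name these as inputs for the definitive trial's sample size.

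The cost is a few sentences of analysis wording and additional table rows. Recruitment, randomisation and the test itself stay as they are. The downside is imprecision: with about 6 completers per sex per arm, the by-sex SDs carry the wide intervals shown above. They should be presented with those intervals and not tested, and the pooled figure should stay in the report.
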